#### Inclusion and exclusion criteria

Inclusion:

• Age 12–20 years

• Diagnosis of BED according to age-adapted DSM criteria;

• BED (DSM-IV-TR): At least 2 days with objective and/or subjective episodes of binge eating per week over the past 6 months; at least 3 out of 5 behavioral indicators; marked distress; absence of regular compensatory behaviors to avoid weight gain; absence of anorexia nervosa and BN;

• BED (DSM-5): At least 1 episode of objective and/xor subjective episodes of binge eating per week over the past 3 months; at least 3 out of 5 behavioral indicators; marked distress; absence of regular compensatory behaviors to avoid weight gain; absence of anorexia nervosa and BN;

• Subthreshold BED (DSM-5). All DSM-5 criteria for BED are met, except the binge eating occurs on average less than once a week and for less than 3 months.

• Written informed consent of parent and adolescent for adolescents ages <18 years, written informed consent of adolescents at ages ≥18 years.

Exclusion:

• Current BN;

• Current substance abuse;

• Current suicidal ideation;

• Psychotic disorder;

• Bipolar disorder;

• Serious unstable medical problems or conditions (e.g., type 1 diabetes mellitus or thyroid problems);

• Current intake of antipsychotic or weight-affecting drugs;

• Current psychotherapy;

• Inpatient psychiatric treatment within the past 3 months prior to screening;

• Current conservative weight loss treatment;

• Female adolescents in pregnancy or lactation;

• Lack of compliance with major study procedures;

• Current participation in another treatment trial.

### Ethical approval

The study was approved by the Ethical Committee at the University of Leipzig Medical Center. Written informed consent of at least one parent and informed consent of the adolescent are obtained for adolescents <18 years after the study has been fully explained. For adolescents ≥18 years, written informed consent of the adolescent only is required. Patients and their parents can withdraw at any point without any penalty. The trial will be conducted in accordance to the guidelines for Good Clinical Practice [51]. All persons participating in the conduct of the trial commit themselves to the Declaration of Helsinki (Version Somerset West 1996) [52], as well as all pertinent national laws and the International Conference on Harmonization guidelines for Good Clinical Practice and CPMP/ICH/135/95 (Note for Guidance on Good Clinical Practice) [53].

### Recruitment

The ongoing study is conducted from September 2011 at the Outpatient Unit of the Integrated Research and Treatment Center (IFB) AdiposityDiseases at University of Leipzig Medical Center, Leipzig, Germany. Recruitment strategies include population-based recruitment (e.g., information letters to households with children in the targeted age range, website http://www.ess-stress.de), school-based recruitment (e.g., educational classes, screening), and recruitment in clinical settings (e.g., IFB Outpatient Unit, behavioral weight loss facilities).

### Procedures

Adolescents are screened by telephone for eligibility in the study. Eligible adolescents and at least one parent are invited to the IFB Outpatient Unit for a diagnostic visit. At the outset of this visit, informed consent is gathered in a written format as described. At baseline assessment, inclusion and exclusion criteria are evaluated using the clinical interviews described below. Additionally, sociodemographic, anamnestic, anthropometric, and clinical data, and health economic parameters, are obtained using interviews, self-report-questionnaires, and objective measurement as described below. After baseline assessment, included patients are centrally randomized into the CBT or WL arm. Following randomization into the CBT arm, patients are offered treatment over 4 months. Following randomization into the WL arm, patients are invited to CBT over 4 months, after a waiting-list period of 4 months.

### Intervention

#### Experimental intervention – Cognitive-behavioral therapy (CBT)

An age-appropriate CBT manual was developed in order to target the above-mentioned psychopathology and maintenance factors of BED in adolescents. This adapted manual was based upon the existing evidence-supported adult manual “Binge eating and obesity: Manual for the treatment of binge eating disorder” by Hilbert and Tuschen-Caffier [54]. This manual for adult BED was piloted in an RCT [55] and is currently used in a multicenter RCT comparing it to Internet-based guided self-help [56]. Recovery and clinically significant improvement rates of the pilot data lay within the range of those determined by other clinical trials evaluating the efficacy of CBT in the treatment of BED [40].

The age-adapted manual for adolescents with BED differs from the adult manual in several aspects: greater focus on less complex, motivating behavioral exercises; decreased focus on cognitive interventions; concentration on age-specific maintenance factors (e.g., difficulties in identity development) including familial factors (e.g., familial eating patterns, family conflict); and a greater focus on enhancing an autonomous motivation for treatment, since adolescents may not necessarily be motivated for treatment and/or treatment may be sought by third parties (e.g., parents).

All adolescent patients are guaranteed confidentiality regarding their parents unless they provide information that meets criteria for mandated reporting. Although family-based treatment is efficacious in adolescent BN [57], parental involvement in adolescent treatment for bulimic eating disorders may decrease compliance [46,50]; thus, treatment is individually focused on adolescents. Parents receive standardized information letters about BED, general intervention topics, and recommendations for daily routine on a monthly basis.

The age-adapted CBT manual includes the following phases: (1) initial treatment phase for motivational enhancement; (2) intensive treatment phase including modules on eating behavior, body image, and stress; and (3) self-management phase for relapse prevention. Therapeutic phases, goals, and techniques are depicted in Table 1.

**Table 1 T1:** Therapeutic phases, goals, and techniques

	**Therapeutic goals**	**Techniques**
	**Initial treatment phase (Sessions 1 – 3)**	
**Initial contact and cognitive preparation**	- To establish a positive therapeutic alliance	- Exploration
	- To enhance motivation	- Information on disorder and treatment
	- To plan therapy	- Goal setting
		- Self-monitoring of eating behavior
		- Self-management and self-reinforcement
	**Intensive treatment phase (Sessions 4 – 18)**	
**Eating behavior module “My Nutrition”**	- To establish a healthy eating behavior	- Information on nutrition and physical activity
		- Self-monitoring of eating behavior and physical activity
		- Goal setting
		- Stimulus and response control
		- Cue exposure
		- Eating hedonics exercises
		- Self-management and self-reinforcement
		- Cognitive restructuring
		- Homework
**Body image module “My Body”**	- To establish a positive body image and weight maintenance	- Information on body image and weight-related stigmatization
		- Body image exposure
		- Self-monitoring of negative body talk
		- Self-monitoring of physical activity
		- Shaping of regular physical activity
		- Body hedonics exercises
		- Self-management and self-reinforcement
		- Cognitive restructuring
		- Homework
**Stress module “My Emotions”**	- To identify and treat related psychopathology (e.g., emotion regulation difficulties, stress management problems, interpersonal conflict, social competence deficits, identity problems)	- Behavioral analysis
		- Information
		- Goal setting
		- Stimulus and response control
		- Role play
		- Problem solving
		- Exposure
		- Self-management and self-reinforcement
		- Cognitive restructuring
		- Homework

#### Control intervention – waiting list (WL)

Half of the patients will be randomly assigned to a WL control condition. All WL patients are guaranteed individual CBT after a waiting period of 4 months (equal to the duration of CBT). The WL patients are instructed not to seek any other medical or psychological treatment for BED or obesity during the WL period without informing the project leader.

### Measures

#### Primary and secondary outcomes

The primary outcome measure is the number of binge eating episodes over the previous 28 days 4 months after randomization (post-CBT, post-WL), which is a standard measure within treatment trials of adult BED [40]. The number of binge eating episodes is assessed with the German version of the Eating Disorder Examination (EDE) [58-60], a validated semi-structured interview regarded as the gold standard for the diagnosis and psychopathological assessment of eating disorders. If necessary, age-adapted language is used from the child version of the EDE [61,62]. For adult BED, it is common to determine the difference in the number of episodes or days with objective binge eating between baseline and follow-up and test for a difference between a treatment and control group [40]. In adolescents, this measure has severe disadvantages since the large variance in the number of episodes with binge eating (i.e., objective and objective binge eating [47,48]) can result in imbalances between randomized arms (e.g., [47]). Abstinence rates, another typical measure in treatment trials for adult BED [40], have the disadvantage that patients who reduce their binge eating substantially, but not completely, are treated as failures. Hence, we chose to consider the ratio of the number of binge eating episodes at 4 months after randomization to the number at baseline as primary outcome criterion.

Secondary outcome measures include the number of binge eating episodes 2 months after randomization (mid-CBT, mid-WL), and maintenance of treatment success regarding the number of binge eating episodes at 6 and 12 months following CBT (6-fu CBT, 12-fu CBT). Additional secondary outcomes are also measured at 2 and 4 months after randomization and at 6 and 12 months following CBT: the number of days with binge eating; abstinence (i.e., zero binge eating episodes) from binge eating; eating disorder psychopathology (all determined through the EDE); additional aspects of non-normative eating behavior as determined through the Dutch Eating Behavior Questionnaire [63,64]; the severity of depressive symptoms [65,66]; self-esteem [67,68]; quality of life [69,70], and body mass index (BMI, kg/m^2^). Body weight and height is objectively measured through calibrated instruments. Psychiatric comorbidity is determined per structured clinical interview K-DIPS [71] 6 and 12 months following CBT.

We chose these outcome measures because they exhibit good psychometric properties in the respective age group, are well-established in German, and are used in international research studies. The structured clinical interviews EDE and K-DIPS are conducted by trained raters. All raters are blind to study hypotheses and randomization, and have no therapeutic relationship with the patients. They underwent extensive training for conducting the interviews and receive ongoing supervision for standardized administration (drift prevention).

#### Cost effectiveness

Health resource utilization and loss of productivity is assessed using the Client Sociodemographic and Service Receipt Inventory [72], adapted for the purposes of this study. The self-report questionnaire is administered at all assessment time points specified above.

#### Predictor variables

Potential predictor variables, assessed at baseline, consist of outcome variables, sociodemographic and anamnestic variables, and patient motivation and expectation ratings assessed through visual analogue scales. The predictor (moderator) variables will be selected based on the literature or on our theoretical understanding of the mode of action of the treatment.

#### Process variables

For exploratory identification of mediators, process measures are obtained by the patient every week of treatment. These consist of a selection of items of the self-report form of the EDE, the Eating Disorder Examination-Questionnaire [73-75].

### Methodological aspects

#### Power analysis

RCTs analyzing the reduction of binge eating episodes by interpersonal psychotherapy [48], an Internet-based CBT program [47], and adolescent-specific CBT [46] provide rough estimates for baseline situations and treatment effects. In these studies, variances in the number of binge eating episodes are large and abstinence rates vary considerably. Simulation of treatment effects that was repeated 5,000 times demonstrated that a power of 95% can be reached with n = 27 individuals per group using a *t*-test (α = 0.05). With an assumed overall dropout rate of 10% of study patients (range: 0 to 11.5%) [47,48], 30 patients should be recruited per study group. While assuming this dropout rate, every effort is made to retain as many participants as possible throughout the period of the study, including providing information to participants on the relevance and necessity of the study, the use of continuity forms locating participants throughout the study period, and use of incentives for follow-up assessments.

#### Randomization

Adolescents who meet the respective criteria and who give informed consent (and for adolescents aged <18 years whose parents give informed consent) are randomized. To ensure concealment of allocation, the randomization is centrally performed by the Coordination Center for Clinical Trials of the University of Leipzig. Randomization is computer-assisted, using Pocock’s minimization algorithm [76]. The randomization is stratified by sex and age (12 to 15 and 16 to 20 years). The allocation ratio between the two arms of the study is 1:1.

#### Blinding

Outcome assessments are performed by independent raters who have no therapeutic relationship with the patients and are blind to study hypotheses and randomization. Blinding of patients and treatment is not possible in this trial, as both therapists and patients know the study arm from the particular modes of delivery.

#### Data analytic plan

The primary outcome “reduction in the number of binge eating episodes over the previous 28 days 4 months after randomization” will be investigated with analysis of covariance using the ratio as the dependent variable (the number of binge eating episodes at 4 months following randomization divided by the number at baseline), treatment group as factor and the inverse number of binge eating episodes at baseline as a covariate based on the full analysis set [77]. The full analysis set includes all randomized patients, regardless of whether or not they provide data at follow-up. Further, the analysis of the number of binge eating episodes will be performed in the per protocol set to evaluate the treatment effect for patients with good protocol adherence. In addition, the maintenance of treatment effects regarding the number of binge eating episodes will be analyzed in the framework of random coefficients modeling. Random coefficients modeling is state of the art in the analysis of eating disorder treatment effects, as it can incorporate heterogeneity of effects (by treatment moderator) and is tolerant of missing data.

Secondary outcome measures will be analyzed in an exploratory manner and will be evaluated by means of parametric or non-parametric tests, depending on the given scale level and type of distribution of the observed variables. Maintenance of treatment effects will be evaluated by random coefficient models. For all outcomes, effect sizes will be estimated and presented with 95% confidence intervals. Predictors of treatment outcome (moderators and mediators) will be identified in an exploratory manner using multivariable analyses.

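### Allocation is minimised on sex and age group, but the primary ANCOVA omits both; if they predict the outcome, its standard error is somewhat too large and its test conservative

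*Protocol article*

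**What the plan says.** The Randomization section of the protocol article states: "Randomization is computer-assisted, using Pocock’s minimization algorithm [76"]. It then names the balancing factors: "The randomization is stratified by sex and age (12 to 15 and 16 to 20 years"). Allocation is 1:1.

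The Data analytic plan section specifies the primary model term by term. It is an "analysis of covariance using the ratio as the dependent variable" (the count of binge eating episodes at 4 months divided by the baseline count), with "treatment group as factor and the inverse number of binge eating episodes at baseline as a covariate", in the full analysis set. The per-protocol set is used for a further analysis of episode counts. Neither sex nor age group is listed as a model term, and no reason is given for leaving them out.

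The Power analysis section sizes the trial on a comparison that also ignores the two factors: "power of 95% can be reached with n = 27 individuals per group using a *t*-test (α = 0.05").

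**The concern.** Minimisation keeps the arms alike on sex and age group. If those factors predict the outcome, balancing removes most of their contribution to the chance difference between arms. A model without them still counts the variance they explain as residual error. Its standard error then describes a simple randomisation that was not used, and exceeds the true sampling variability of the estimate.

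At stake are the validity of the reported interval and p-value, and some power, in a trial that expects about 27 analysable patients per arm and describes the variance of its outcome as large.

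**Working it through.** **Inputs from the article.** Minimisation on two binary factors; 1:1 allocation; primary model with arm and inverse baseline count; 27 per group for 95% power at α = 0.05; 10% dropout; 30 recruited per group.

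**The plan's own figures.** 27 / (1 − 0.10) = 30 per group, as stated. The 95% power comes from a simulation whose effect and standard deviation are not given, so it can only be solved backwards. With a noncentral t on 52 degrees of freedom, 95% power at 27 per group implies d = 1.00 (two-sided) or d = 0.91 (one-sided; the article does not state sidedness).

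**Limiting case, perfect balance.** Let R² be the share of outcome variance explained by sex and age group. The planned model reports a variance proportional to σ², while the true variance of the estimate is proportional to σ²(1 − R²). The type I error of the nominal 5% test is then 2 × (1 − Φ(1.96 / √(1 − R²))):

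- R² = 0.05: 4.4%
- R² = 0.10: 3.9%
- R² = 0.20: 2.8%

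These are bounds, because minimisation does not balance perfectly.

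**Simulation.** The assumptions were N = 54 (2 × 27), minimisation with a biased-coin probability of 0.8, factor splits of 80%/50%, a normal outcome and two-sided α = 0.05, with 5,000 runs per setting. Effects are in outcome standard deviations. The Monte Carlo standard error of a 5% rejection rate is √(0.05 × 0.95 / 5000) = 0.3 points. The value d = 0.74 is an illustrative smaller effect and is not in the article. Standard errors in the table are from the runs with no treatment effect.

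| R² | Reported SE, planned model | Empirical SE, planned model | Type I: planned → with factors | Power at d = 0.74: planned → with factors | Power at d = 1.0: planned → with factors |
|---|---|---|---|---|---|
| 0 | 0.273 | 0.272 | 0.049 → 0.049 | 0.762 → 0.757 | 0.945 → 0.944 |
| 0.05 | 0.273 | 0.269 | 0.045 → 0.048 | 0.750 → 0.762 | 0.950 → 0.956 |
| 0.10 | 0.274 | 0.265 | 0.042 → 0.052 | 0.757 → 0.790 | 0.954 → 0.965 |
| 0.20 | 0.274 | 0.250 | 0.033 → 0.051 | 0.775 → 0.839 | 0.960 → 0.977 |
| 0.30 | 0.274 | 0.237 | 0.025 → 0.053 | 0.780 → 0.879 | 0.963 → 0.988 |

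The planned model's standard error is too large by 0.274 / 0.265 = 1.03 (3%) at R² = 0.10 and 0.274 / 0.250 = 1.10 (10%) at R² = 0.20. With the factors in the model, reported and empirical standard errors agree: 0.260 and 0.263 at R² = 0.10, and 0.245 and 0.246 at R² = 0.20.

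**Interval width is not power.** The reported variances differ by (0.274 / 0.260)² = 1.11 and (0.274 / 0.245)² = 1.25. The estimates themselves are almost equally precise: empirical SE 0.265 without the factors and 0.263 with them at R² = 0.10, and 0.250 and 0.246 at R² = 0.20. Under perfect balance, the extra patients that the planned test needs to match the adjusted test at 95% power are ((1.96 / √(1 − R²) + 1.645) / (1.96 + 1.645))² − 1:

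- R² = 0.05: about 3%
- R² = 0.10: about 6%
- R² = 0.20: about 13%

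**The case against.** The strongest reply is that the harm is assumed. The article nowhere says that sex or age group predicts the ratio of 4-month to baseline episodes. The R² that matters is what remains after inverse baseline is in the model. With episode counts as variable as the article describes, a 10% to 20% share for two binary factors may be optimistic. This stands: the size is conditional, and at R² = 0.05 the simulated type I error is barely distinguishable from 5%.

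The error is also on the safe side, and the planned power is not endangered. At d about 1 the planned model keeps about 95% power at every R² examined. This stands too.

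It could further be said that a condensed article leaves covariates to the analysis plan. That does not carry here, because the article spells out the dependent variable, factor, covariate and analysis set. A later plan that added sex and age group would change the stated primary model. The absence of a re-randomisation test or an adjusted sensitivity analysis is different. An article may properly leave those to the analysis plan, and they are not counted against it.

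**Conclusion.** The mismatch between allocation and primary model is explicit in the text, and its direction is clear: if sex and age group are prognostic, the interval is too wide and the test conservative. The size is modest. For assumed R² of 0.05, 0.10 and 0.20, type I error is about 4.5%, 4.2% and 3.3%. For R² of 0.10 to 0.20, adjusting gains about 1 to 2 points of power at d about 1 and about 3 to 6 points at d = 0.74. At R² = 0 nothing measurable is gained or lost. These figures rest on the simulation settings listed above, none of which the article supplies beyond the sample size, the two factors and the allocation method.

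Three stronger readings are not supported:

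- A reader might infer that the primary result would be biased or its false-positive rate inflated. The test errs in the opposite direction.
- A reader might take 1 / (1 − R²) − 1, that is 5%, 11% or 25%, as the number of patients wasted. That ratio describes reported variance. In terms of power at 95% the figure is about 3%, 6% or 13%, even under perfect balance.
- A reader might extend the point to every secondary analysis. Those are declared exploratory and may be non-parametric, so exact type I calibration has little force there.

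**What to change.** Add sex and age group (12 to 15, 16 to 20) as fixed factors to the primary analysis of covariance and to its per-protocol repeat. State this before outcome data are released. The article plans no interim analyses and holds post-treatment data until the study is complete, so the change can be made without knowledge of outcomes.

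The cost is one sentence and two degrees of freedom, with no new data and no change in sample size. A re-randomisation test that follows the minimisation procedure is an optional check of the p-value. The exploratory secondary tests need not change.

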## Methods/design

### Hypotheses

(1) Age-adapted individual CBT will be superior to WL in reducing the number of binge eating episodes in adolescents with BED 4 months following randomization.

(2) Age-adapted individual CBT will be superior to WL in reducing the number of days with binge eating episodes; leading to greater abstinence from binge eating; reducing eating disorder psychopathology and the severity of depressive symptoms; increasing self-esteem and quality of life; and stabilizing body mass index. The therapeutic gains will occur at mid-treatment and will be maintained at 6 and 12 months following CBT.

(3) Age adapted individual CBT will be cost-effective.

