### Design, participants, and procedures

#### Study design

BEDA is a single-center, prospective, randomized superiority trial, evaluating the efficacy and cost-effectiveness of CBT (experimental condition) compared to a WL control condition. The study design is depicted in Figure 1. The study period lasts 4 months per patient in the experimental condition (4 months of CBT) and 8 months in the control condition, including 4 months of WL and 4 months of CBT; each patient is offered individual CBT. Using an observer-blind design, patients are assessed at baseline, 2 months after randomization (mid-CBT; mid-WL), 4 months after randomization (post-CBT; post-WL or pre-CBT/WL), and at 6- and 12-months follow-up after the end of treatment (6-fu CBT, 12-fu CBT; 6-fu CBT/WL, 12-fu CBT/WL). The patients in the WL condition are assessed additionally 2 months (mid-CBT/WL) and 4 months (post-CBT/WL) after the end of the waiting period (i.e., after post-WL or pre-CBT/WL).

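### The tests stated for the exploratory secondary outcomes at months 2 and 4 name no baseline adjustment and leave the reported effect open until the data are seen

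*Protocol article*

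**What the plan says.** The Data analytic plan gives three different treatments.

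- **Primary outcome:** an analysis of covariance of the ratio of month-4 to baseline episodes, with "the inverse number of binge eating episodes at baseline as a covariate".
- **Maintenance:** "Maintenance of treatment effects will be evaluated by random coefficient models".
- **Other comparisons of secondary outcomes:** "Secondary outcome measures will be analyzed in an exploratory manner", and they "will be evaluated by means of parametric or non-parametric tests, depending on the given scale level and type of distribution of the observed variables". No baseline covariate and no change score is named.

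It adds: "For all outcomes, effect sizes will be estimated and presented with 95% confidence intervals".

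The baseline data exist. Under Study design, "patients are assessed at baseline, 2 months after randomization (mid-CBT; mid-WL), 4 months after randomization"; under Predictor variables, "Potential predictor variables, assessed at baseline, consist of outcome variables". The second hypothesis is worded largely as change, for example "increasing self-esteem and quality of life; and stabilizing body mass index".

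**The concern.** Where the authors intend a model, they name it. For the secondary outcomes they name a rule for choosing a test, and the ordinary reading of that rule is a two-group comparison.

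Waiting-list patients receive CBT after month 4, so months 2 and 4 are the only visits at which the randomised arms can be compared untreated against treated. The random coefficient models are stated for maintenance, so they do not clearly cover these visits.

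Two things are at stake.

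- **Precision.** With about 27 evaluable patients per arm, an unadjusted comparison of depression, self-esteem, quality of life, eating disorder psychopathology or BMI gives wide intervals. Chance differences at baseline pass into the estimate. Minimisation balances sex and age group only.
- **The effect being estimated.** A t-test addresses a difference in means and a rank test a shift in distribution. If the observed distribution decides between them, the effect size promised with its interval is settled only once the data are in hand.

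**Working it through.** **Inputs from the protocol article.** 27 evaluable per group, α = 0.05 and 10% dropout (Power analysis); 1:1 allocation (Randomization). Two-sided testing is assumed, because sidedness is not stated.

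**Inputs not in the document (assumptions).** The correlation ρ between baseline and follow-up: 0.4 to 0.7 for the scales, 0.9 or above for BMI. The SD of BMI: 7 kg/m².

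**The plan's own figure.** 27 / (1 − 0.10) = 30 per group, as stated. The 95% power cannot be recomputed, because the effect and SD used in the simulation are not given. With a two-sided t-test, 27 per group at 95% power implies a difference of about 1.00 SD. That figure concerns the primary outcome; none is given for the secondary outcomes.

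**Variance relative to a post-score test.** ANCOVA: 1 − ρ². Change score: 2(1 − ρ).

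| ρ | ANCOVA | Removed by ANCOVA (ρ²) | Change score |
|---|---|---|---|
| 0.4 | 0.84 | 16% | 1.20 |
| 0.5 | 0.75 | 25% | 1.00 |
| 0.7 | 0.51 | 49% | 0.60 |
| 0.9 | 0.19 | 81% | 0.20 |
| 0.95 | 0.0975 | 90% | 0.10 |

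More than half is removed only if ρ² > 0.5, that is ρ > 0.71. For a scale at ρ = 0.5, a change score gains nothing over the post score; at 0.4 it is worse.

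**Power for a true difference of 0.5 SD** (noncentral t, 27 per arm; the adjusted standardised difference is 0.5 / √(1 − ρ²)):

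- post score: 44%
- ANCOVA, ρ = 0.5: 0.5 / 0.866 = 0.577, giving 55%
- ANCOVA, ρ = 0.7: 0.5 / 0.714 = 0.700, giving 71%

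**BMI, SD 7.** The standard error of the arm difference in post scores is 7 × √(2/27) = 1.91 kg/m², so the 95% interval is about ±3.8 kg/m² (t = 2.007).

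| ρ | SE, ANCOVA: 1.905 × √(1 − ρ²) | SE, change: 1.905 × √(2(1 − ρ)) |
|---|---|---|
| 0.9 | 0.83 | 0.85 |
| 0.95 | 0.595 | 0.602 |

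Power for a 1 kg/m² difference is 8% with post scores. At ρ = 0.95 it is 38% with ANCOVA and 37% with change scores. At ρ = 0.9 it is 22% and 21%.

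**Choice of test from the data.** A simulation (4,000 runs, 27 per arm, no true difference) chose between t-test and Mann-Whitney by a Shapiro pre-test. The type I error was 4.9% for normal and 4.4% for lognormal data, so there was no inflation.

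**The case against.** The strongest objection is that the loss is inferred from silence. The sentence does not say that baseline is left out. ANCOVA is itself a parametric analysis, and the second hypothesis, worded as change, fits change scores. The model for each secondary outcome is also usual content of an analysis plan that is not shown, and these analyses are declared exploratory.

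Much of this stands. A reader might infer that the plan discards the baseline values; the text does not support that, only that no adjustment is named. The point still survives as more than missing detail, because the article states a selection rule for these outcomes, and that rule depends on the observed distribution. A prespecified adjusted model is better than that rule under any reading, although for BMI by very little if change scores were meant.

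Four other strong readings are tempting and should not be made.

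- **Most of the information is wasted for the scales.** That needs ρ above 0.71; at 0.4 to 0.7 the loss is 16% to 49%.
- **The protocol itself warns of baseline imbalance for these outcomes.** Its remark under Primary and secondary outcomes concerns the number of binge eating episodes only. It may plausibly extend to binge days, but it says nothing about BMI or the questionnaires.
- **Choosing the test from the data inflates false positives.** The simulation shows no such effect.
- **Rank tests cannot supply the promised intervals.** They can, for example by Hodges-Lehmann. The difficulty is only that the effect is not fixed in advance.

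**Conclusion.** The point holds in a limited form. For the exploratory arm comparisons at months 2 and 4, the article names a data-dependent choice of test and no baseline adjustment, although the baseline values are collected. If post scores are compared, the result is unbiased but less precise than it need be: by 16% to 49% of the variance for the scales at ρ 0.4 to 0.7, and by 81% or more for BMI at ρ 0.9 or above. The correlations and the BMI SD are assumptions, since the document gives neither. If change scores were meant, little of the BMI gain remains, while for scales with ρ near 0.5 or below change scores bring no benefit.

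The choice between a mean-based and a rank-based test also leaves the reported effect unfixed. The argument does not carry over directly to abstinence, because patients enter with binge eating and abstinence therefore has no informative baseline value of its own. The primary analysis is not touched. The change should be made, but the trial's validity does not depend on it.

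**What to change.** Under Monitoring and data management, post-treatment data are released only after the 12-month follow-up. Before that release, write one model per outcome into the analysis plan.

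- **BMI, eating disorder psychopathology, eating behaviour, depressive symptoms, self-esteem and quality of life:** ANCOVA, or a mixed model over months 2 and 4, on the score itself. Include its own baseline value and the minimisation factors sex and age group. Report the adjusted mean difference with its 95% interval, using robust or bootstrap intervals where residuals are skewed, and do not switch tests.
- **Days with binge eating:** a baseline-adjusted model suited to a count bounded at 28, taking the 28-day window that the protocol states for episodes. An unbounded count model such as the negative binomial does not respect that limit.
- **Abstinence:** adjustment for the baseline number of episodes is optional.

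Keep the exploratory label. If the full analysis plan already specifies such models, it is enough to say so in reporting. The cost is analysis wording only; no new data, visits or patients are needed.
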